## Enablement

We will also use the Patient Enablement Instrument (PEI) that is designed to capture patients' ability to understand the nature of their problems and cope with their illness (Howie 1998). It was developed in primary care to be completed by the patient after a consultation. We will adapt it to rate patient enablement at the 6-month follow-up, looking back over the whole period of the intervention, as was done successfully in the ATEAM trial (Little 2008), when the adapted measure proved sensitive to change.

## Costs

A societal perspective will be taken for the health economics analysis. Bespoke questionnaires, developed in light of the WS1 systematic review and WS2 qualitative interviews, and modified in light of the experience of using them in WS4, will be used to collect data on health and social service resource use; personal out of pocket spending; and time off work.

In addition, a review of patients' computerised GP records will be conducted by practice staff to extract any additional health service usage including medication, primary care consultations, outpatient appointments, A&E attendances, and hospital admissions. All items will be costed using appropriate data (e.g. British National Formulary, Personal Social Service Research Unit (PSSRU) and NHS reference costs), with informal care costed at minimum wage level.

The resource use questionnaire will be administered face to face with patients at baseline, 6 and 12 months, asking them to look back over the previous 6 months at each point. The case note review will be done by general practice staff looking back over the previous six months from the six-month follow-up point, and again from the end of the 12 months follow-up.

## Consent and data collection summary

| Measure | Reply slip | Screening (telephone) | Baseline (Remote/face to face) | 3 months (postal or on-line) | 6 months (Remote/face to face) | 9 months (postal) | 12 months (Remote/face to face) |
|---------|------------|-----------------------|--------------------------------|------------------------------|--------------------------------|-------------------|---------------------------------|
|---------|------------|-----------------------|--------------------------------|------------------------------|--------------------------------|-------------------|---------------------------------|

|                                                                                                                |   |   |   |   |   | or on-line) |   |
|----------------------------------------------------------------------------------------------------------------|---|---|---|---|---|-------------|---|
| Consent to be contacted about the study                                                                        | ✓ |   |   |   |   |             |   |
| Inclusion/exclusion criteria                                                                                   |   | ✓ |   |   |   |             |   |
| Consent to participate                                                                                         |   |   | ✓ |   |   |             |   |
| Sociodemographics and past history of depression questionnaire                                                 |   |   | ✓ |   |   |             |   |
| Depression (PHQ-9)                                                                                             |   | ✓ | ✓ | ✓ | ✓ | ✓           | ✓ |
| Anxiety (GAD-7)                                                                                                |   | ✓ | ✓ | ✓ | ✓ | ✓           | ✓ |
| Suicidal ideas                                                                                                 |   | ✓ | ✓ | ✓ | ✓ | ✓           | ✓ |
| Discontinuation of antidepressants (for at least 2 months, by 6 months)                                        |   |   |   |   | ✓ |             |   |
| Quality of life (EQ-5D, SF-12)                                                                                 |   |   | ✓ | ✓ | ✓ | ✓           | ✓ |
| Wellbeing (WEMWBS)                                                                                             |   |   | ✓ |   | ✓ |             | ✓ |
| Withdrawal symptoms (DESS)                                                                                     |   |   | ✓ | ✓ | ✓ |             |   |
| Antidepressant side effects (ASEC, CSFQ-C) (if taken)                                                          |   |   | ✓ |   | ✓ |             | ✓ |
| Satisfaction (MISS-29)                                                                                         |   |   |   |   | ✓ |             | ✓ |
| Enablement (PEI)                                                                                               |   |   |   |   | ✓ |             | ✓ |
| Questionnaires on use of services, use of antidepressants, sickness absence, and beliefs about antidepressants |   |   | ✓ |   | ✓ |             | ✓ |
| Collective efficacy questionnaire                                                                              |   |   |   | ✓ |   |             |   |

## STATISTICAL ANALYSIS

Intention to treat (ITT) analyses at patient level will be performed, using mixed logistic/linear regression models, controlling for baseline values, stratification variables, and potential confounders as appropriate. Practice will be modelled as a random effect to allow for the clustering of patients within practices. Patterns of missing data will be explored, sensitivity analysis used to explore the impact of missingness, and imputation of missing data will be used. In a non-inferiority trial where some patients do not comply with treatment as randomised, the difference between the arms can appear reduced and the groups look more similar, leading to the incorrect conclusion of non-inferiority. A per protocol (PP) analysis would analyse individuals based on their compliance with treatment as randomised, excluding non-compliant participants, giving a more conservative estimate of effect for non-inferiority (Piaggio 2006).

However, the exclusion of some participants after randomisation can potentially lead to bias. Therefore we will present both ITT and PP analyses.

We will also undertake a complier-average causal effect (CACE) analysis, another approach to dealing with noncompliance that compares compliant participants in the intervention group, with those in the control group whose characteristics are similar enough to the intervention group compliers to suggest they too would have complied with the intervention, given the opportunity to do so (Angrist 1996, Dunn 2005). Compliance for these analyses in the intervention arm will be defined as completing the first session of the LifeGuide programme within 6 months of recruitment (anticipating 90% plus). The first session will have information about antidepressant treatment, the rationale for attempting withdrawal, and how withdrawal should be attempted under supervision. We would expect patients to benefit from that session even if they do not log on again. Compliance in the control arm will be defined as having consulted the GP/PN to have their antidepressant treatment reviewed within the 6-month follow-up period. For the primary outcome we will report the analyses based on all three approaches and interpret the findings cautiously in light of any differences between approaches that may emerge. This analysis will form the core of the publication of the trial results. No interim analyses will be performed.

For secondary outcomes the analyses will use a similar modelling approach to that set out for the primary outcome, with mixed logistic/linear regression models as appropriate, with a random effect for Practice, controlling for baseline values, stratification variables, and potential confounders as appropriate. Discontinuation of antidepressants will be evaluated at the 6 month time point. All other secondary measures will be analysed using a repeated measures approach with measures clustered within patients over time in addition to the clustering of patients within practice. The models will control for stratification variables, and potential confounders as appropriate and, where a baseline measure for the outcome is available, will for the baseline value, too.

A detailed statistical plan will be developed and discussed with the Independent Data Monitoring Committee and Programme Steering Committee (see below).

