## Consent procedure

The researcher will arrange to meet the patient, either remotely, or at their GP practice, or at their home if they prefer, to go over the consent procedure. If the patient gives verbal and then subsequent written consent to take part, the researcher will conduct a baseline assessment. Information given at the point of consent will be the same in both arms. All patients will be told we are recruiting people who have been taking antidepressants for more than a year for a first episode, or more than two years for a recurrent episode, with a view to working out how to help them reduce their medication if appropriate, with the advice of their practice GP or nurse (see patient information leaflet and consent form). The information leaflet will outline the two different approaches but not in detail and potential participants will not know to which arm their general practice has been randomised. This is to avoid differential rates of consent to the two arms based on patients' opinions of the intervention or procedures involved in each.

Patients who do not wish to consent to take part at that point for reasons which may be temporary (i.e. they do wish to try to reduce and stop taking their antidepressant, but not at that time due to current life stresses, recent life events, or the timing of upcoming events etc.), will have the option of consenting to be re-contacted after three months, to be asked again if they wish to participate at that later point.

Having once consented to take part in writing on this initial basis, and having undergone baseline assessment, patients will then be given further information about the details of the procedures in the arm to which their practice has been randomised. In the intervention arm, patients will be given advice and support to log on and engage with their web-based support (see below). After looking at the on-line ADvisor for patients, they will be asked to arrange to consult with their GP/NP either remotely or in person to discuss coming off antidepressants, including agreeing a time to start tapering the dose, and a first follow-up appointment for review.

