### Sample size calculation

We originally calculated that, to have 90% power, with a one-sided alpha of 2.5%, to establish non-inferiority in terms of depressive symptoms within 2 points (MCID) on the PHQ-9 at 6 months (SD 5.4), we needed 155 patients followed up in each arm. Assuming a variable cluster size of between 1 and 7 per practice (mean 3) and an intra-cluster correlation coefficient (ICC) of 0.012 (from the HTA THREAD trial of treating mild to moderate depression in primary care, [name] 2009) gave a 1.033 cluster design effect (based on a coefficient of variation of  $1.5/3=0.5$ , using the formula in Eldridge 2006). Anticipating 20% do not comply with the intervention and/or are lost to follow up, we needed to randomise  $(155 \times 2 \times 1.036) / 0.8 = 402$  patients (201 per arm), from 134 practices (67 per arm).

However we found (in May 2021) a significant correlation between baseline and follow-up values for the primary outcome (the PHQ-9 score at 6 months) of 0.47 (95% confidence interval 0.26 to 0.63). Assuming conservatively that this correlation remains 0.26 or greater until the end of follow-up, the necessary target sample size to give 90% power will be reduced by a deflation factor of  $1 - 0.26^2$  (Borm, 2007) which means we can achieve 90% power to address the research question with a total sample size of 375 patients recruited, given the other parameters in the original sample size calculation remain unchanged. If the current level of correlation of 0.47 persists until the end of follow-up, the sample size needed for 90% power would be reduced to a total recruited of 313 patients. We assumed that the level of correlation was likely to end up somewhere between 0.26 and 0.47 and, with the agreement of the Funder the NIHR, and the Sponsor, the University of Southampton, the target sample size was therefore reduced to 360 patients (May 2021).

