##### **3.1.2 Per-protocol analysis population**

In a non-inferiority trial where some patients do not comply with treatment as randomised, the difference between the arms can appear reduced and the groups look more similar, leading to the incorrect conclusion of non-inferiority. A per-protocol analysis would analyse individuals based on their compliance with treatment as randomised, excluding non-compliant participants, which may give a more conservative estimate of effect for non-inferiority. However, the exclusion of some participants after randomisation can potentially lead to bias. Therefore, we will present both intention-to-treat and per-protocol analyses. The ITT analysis will be the primary and the per-protocol analyses will be treated as secondary.

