##### **3.1.3 CACE analysis population**

We will also undertake a complier-average causal effect analysis, which is another approach for dealing with non-compliance that compares compliant participants in the intervention group with those in the control group whose characteristics are similar enough to the intervention group compliers to suggest they too would have complied with the intervention given the opportunity to do so. Compliance for these analyses in the intervention arm will be defined as completing the first session of the LifeGuide programme within 6 months of recruitment (anticipating >90%). The first session will have information about antidepressant treatment, the rationale for attempting withdrawal, and how withdrawal should be attempted under supervision. We would expect patients to benefit from that session even if they do not log on again.

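### The per-protocol rule counts a prescriber review in the control arm only, accepts a late web session in the intervention arm, and is missing from the SAP

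*Combined protocol and SAP*

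**What the plan says.** The protocol (Statistical Analysis) plans a per-protocol analysis beside ITT because non-compliance can make the arms look alike and so favour non-inferiority. It calls the per-protocol estimate more conservative and accepts that post-randomisation exclusions can cause bias. After introducing the CACE analysis, it defines compliance by arm. For controls, "Compliance in the control arm will be defined as having consulted the GP/PN to have their antidepressant treatment reviewed within the 6-month follow-up period". In the intervention arm the criterion is finishing the first LifeGuide session within 6 months, with 90% or more expected to do so. No expected rate is given for controls.

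SAP 3.1.2 describes the per-protocol approach only in general terms, as "excluding non-compliant participants, which may give a more conservative estimate of effect for non-inferiority", and makes it secondary to ITT. It gives no criterion for either arm. SAP 3.1.3, headed as the CACE population, says "Compliance for these analyses in the intervention arm will be defined as completing the first session of the LifeGuide programme within 6 months of recruitment" and has no control-arm sentence. SAP 4.4 runs the primary model again on the per-protocol and CACE populations and reports all three analyses.

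In the protocol's Consent procedure, intervention patients look at the website and then "they will be asked to arrange to consult with their GP/NP either remotely or in person to discuss coming off antidepressants". Control patients are also asked to book a consultation (Consent procedure; Control arm).

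**The concern.** A per-protocol set should hold patients who received what their arm was assigned. Here a step asked of both arms, the antidepressant review, decides membership in one arm only. A patient who never sees a prescriber is removed if a control, and kept if in the intervention arm with one session finished.

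Two things are at stake. First, the analysis is there to counter dilution, but its intervention criterion is loose in content and in time, so it may remove very little. Second, retained patients are chosen on different behaviours in the two arms, so the per-protocol difference carries a selection effect of unknown sign. It will be read beside the ITT result, so that effect could give false reassurance or create a conflict that is not real. Because the SAP does not state who belongs to the set, membership would have to be settled later, which is what the SAP says it exists to avoid (SAP 1.1).

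**Working it through.** **1. Which analysis the control criterion serves.** It stands in the protocol's CACE paragraph, but the sentence introducing the definitions speaks of analyses in the plural, after both per-protocol and CACE have been described. CACE as described looks for controls who would have complied with the intervention if offered it. Whether a control saw the GP plays no part in that. The control criterion therefore makes sense only for the per-protocol set.

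**2. The criteria side by side.**

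| | Intervention | Control |
|---|---|---|
| Asked to consult GP/nurse | Yes (Consent procedure) | Yes (Consent procedure; Control arm) |
| Protocol compliance criterion | First LifeGuide session within 6 months | Antidepressant review within 6 months |
| Criterion in SAP 3.1.2 | None | None |
| Criterion in SAP 3.1.3 (CACE) | First session within 6 months | None |

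**3. Dilution.** With 90% or more compliant, at most about 10% of the intervention arm is removed. Those kept can include patients with no review, although the Consent procedure has the start of tapering agreed at that consultation. They can also include patients who finish session 1 just before the endpoint. The protocol's Discontinuation section allows up to 4 months for tapering and cessation plus 2 months off drug, 6 months in all. A patient who begins only after a session finished later than month 4 has under 2 months left, so cannot meet the plan's definition of discontinuation by month 6, yet counts as compliant.

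**4. The plan's own sample size.** The inputs (Sample size calculation) are one-sided alpha 2.5%, power 90%, margin 2 and SD 5.4.
- n per arm = 2 × (1.960 + 1.282)² × 5.4² / 2² = 153.2, so 154. The plan says "we needed 155 patients followed up in each arm", which agrees to within one patient.
- 155 × 2 × 1.036 / 0.8 = 401.5, so 402 as stated.

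**5. Size of the selection effect.** The documents give neither a control review rate nor PHQ-9 by compliance, so only a range under assumptions is possible. Take the difference as intervention minus control, with higher values worse. If a share c of controls is excluded and their mean differs from retained controls by D, the difference moves by c × D. If a share ci of the intervention arm is excluded with difference Di, it moves by −ci × Di.

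Assumptions: 360 randomised, 10% lost, 10% of the intervention arm non-compliant with Di = 0, design effect 1.036, and the plan's lower correlation of 0.26. Then:
- residual SD = 5.4 × √(1 − 0.26²) = 5.21
- intervention effective n = 360/2 × 0.9 × 0.9 / 1.036 = 140.7
- control effective n = 360/2 × 0.9 × (1 − c) / 1.036
- SE = 5.21 × √(1/n₁ + 1/n₂)
- error at the margin = Φ(−1.96 − shift/SE)
- power at no true difference = Φ((2 − shift)/SE − 1.96)

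| c | D | Shift | SE | Error at margin | Power |
|---|---|---|---|---|---|
| 10% | −2 | −0.2 | 0.622 | 5.1% | 94% |
| 10% | +2 | +0.2 | 0.622 | 1.1% | 83% |
| 20% | −2 | −0.4 | 0.641 | 9.1% | 96% |
| 20% | 0 | 0 | 0.641 | 2.5% | 88% |
| 20% | +2 | +0.4 | 0.641 | 0.5% | 70% |
| 40% | −3 | −1.2 | 0.695 | 41% | 99.6% |
| 40% | +3 | +1.2 | 0.695 | <0.1% | 21% |

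The extremes are 0.40 × (±3) = ±1.2 points.

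**6. If only the intervention criterion were applied.** No controls leave, so the control mean does not move. With ci = 10% and Di up to ±3, the shift is 0.10 × 3 = 0.3 points either way. At −0.3 the error at the margin is about 7%.

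**The case against.** Arm-specific compliance is not in itself an error: the assigned care differs, and the plan gives a reason for its criterion, namely that the first session covers how to attempt withdrawal under supervision and is expected to help on its own. Both documents warn of exclusion bias, the SAP says only that per-protocol may be more conservative, per-protocol is secondary, and differences between analyses are to be read with care. All of that stands, and it limits the weight of the point. It does not supply the missing definition, nor explain why a step asked of both arms counts in one.

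The range in the working is also generous. SAP 4.4 adjusts for baseline PHQ-9, anxiety, and duration and history of depression, so only the residual difference biases the estimate. Entry is restricted to PHQ-9 below 12 and GAD-7 below 10. Intervention exclusions could offset or add up to 0.3 points.

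A reader might infer three stronger things that the documents do not support:
- **The per-protocol analysis drifts towards non-inferiority.** That needs excluded controls to be less depressed than retained ones, or excluded intervention patients to be more depressed. No document says so, and control attendance is prompted by a record flag and a request to book. The opposite pattern makes the analysis stricter.
- **Exclusions occur in one arm only.** The protocol's rule excludes in both arms. The SAP gives no per-protocol rule at all, so a one-arm reading means importing its CACE criterion. Under that reading no controls leave, and a large shift in the control mean cannot arise.
- **The trial's conclusion depends on ITT and per-protocol agreeing.** No section says this.

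**Conclusion.** The point holds in a limited form. The protocol's criteria differ in kind between arms, and SAP 3.1.2 states none. The intervention criterion keeps patients without a review and patients whose session came too late to matter, so the analysis does little of the job it is there for. This part rests on the text alone.

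The selection effect has no established sign. Its size of about −1.2 to +1.2 points rests on assumed exclusion of 10–40% of controls and an outcome difference of up to 3 points, before covariate adjustment. It is about −0.3 to +0.3 if only the intervention criterion is applied. The primary ITT analysis is untouched. This is a cheap improvement to a secondary analysis.

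**What to change.** In SAP 3.1.2, state the per-protocol rule for both arms and reconcile it with the protocol's Statistical Analysis section:
- In both arms, require a GP or nurse antidepressant review on record between baseline and the 6-month PHQ-9.
- In the intervention arm, also require session 1 to be finished before that review, or by a pre-specified date well ahead of the 6-month assessment.
- Keep the session-1 definition for CACE in SAP 3.1.3.
- Do not presume that the per-protocol result is conservative.
- Report the number excluded and their baseline PHQ-9, by arm.

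The change is mainly to SAP wording. Practice staff already extract primary care consultations from records (Costs), subject to consent (Data collection). The protocol does not say that antidepressant reviews are identified as such, so some work is needed there, but its own control criterion already requires it. The intervention per-protocol set becomes somewhat smaller and its interval slightly wider. Some selection remains if the intervention itself changes who attends a review, which is why exclusions should be reported by arm.
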